### Eligibility criteria {10}

Adults (≥ 18 age) diagnosed with SSD (according to DSM-5) who also exhibit a sufficient level of symptom severity, as indicated by a score ≥ 5 in the Patient Health Questionnaire, somatic symptom version (PHQ-15 [43]), and disability, as indicated by a score ≥ 4 in the (modified) Pain Disability Index (PDI [44]), and who have access to the internet and an internet-capable device, will be eligible for inclusion. The selected PHQ-15 cut-off has been shown to be a suitable marker for identifying individuals at high risk for a diagnosis of SSD in a representative population sample [45]. Similarly, the PDI cut-off has proven to be sensitive to relevant impairments in functional status due to PSS in a population-based survey [44]. Prior to their inclusion in the study, written informed consent will be obtained from all participants (inclusion criteria). Participants who meet at least one of the following exclusion criteria will be unable to enroll in the trial (exclusion criteria): (a) Acute, unstable, or severe physical condition that prevents safe trial participation, (b) inadequate command of the German language (reading and/or speaking) (c) severe substance use disorder (according to DSM-5), (d) acute suicidality or (e) acute psychotic states, (f) parallel psychotherapy or (g) participation in another intervention study. The study therapists will be licensed CBT therapists or clinical psychologists currently undergoing advanced post-graduate CBT training under supervision. Prior to treating study patients, all therapists will complete study-specific training provided by the principal investigator (PI) about SSD, the treatment conditions, and the study procedures. For ethical considerations, the study does not include a no-treatment control group.

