
### Sample size {14}

Short-term CBT has demonstrated predominantly small to medium-sized between-group effects on somatic symptom severity in patients with medically unexplained physical symptoms or somatoform disorders (Standardized Mean Difference; *SMD* = 0.37; [18]) and medium- to large-sized within-group effects (*SMD* = 0.80; [83]), as corroborated by a multicenter CBT trial in outpatients with PSS (Cohen’s *d* = 0.70; [51]). Stand-alone internet-delivered CBT yielded small-sized average between-group effects on this outcome (*SMD* = 0.35; [84]) across chronic pain and functional somatic syndromes, whereas evidence from RCTs in individuals with diagnosed/probable SSD demonstrated medium- to large-sized effects (*d* = 0.68 to 0.91) [57, 85]. Evidence from depression research indicates small to medium-sized effects (*d* = 0.32 to 0.51) [34, 86] of added internet interventions to outpatient psychotherapy, which mirrors the treatment setting in the current study. Taken together, we expect the difference between our blended treatment and the enhanced treatment to be *d* = 0.40 for the primary endpoint. Thus, with a power of 80%, and a significance level of 0.05 (two-sided), 200 patients are required, when using a t-test. Because of some variability in effect sizes in the literature and the multicenter study introducing additional heterogeneity we planned the sample size conservatively by not using any correlation between measurements or between outcome and baseline variables. Based on treatment studies in this research field we expect a study drop-out for our primary endpoint (t1) up to 20% [51, 87], resulting in a sample size of *N* = 250 (125 per group). A study in the same setting concluded a similar sample size of 194 [51]. The calculation was performed with SAS 9.4.

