## Assignment of interventions: allocation

### Sequence generation {16a}

A randomization list is generated at Interdisciplinary Center for Clinical Trials (IZKS) at the University Medical Center Mainz by means of a validated SAS program (9.4 (SAS Institute, Cary, NC, USA)). The randomization ratio of the treatment group and the control group will be 1:1. Randomization will be stratified by study center. Block randomization with different block size will be applied.

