## Statistical methods

### Statistical methods for primary and secondary outcomes {20a}

The *primary endpoint* will be analyzed with a linear mixed-effect model (LMM) including center, use of prescribed psychopharmaceutic (ATC code N06A, yes/no), use of other (non-psychopharmaceutic) medications such as analgesics or antihypertensives (yes/no), mental disorder comorbidity (yes/no), intervention, time point, and the interaction term of intervention and time point as fixed effects, as well as baseline value as a covariate. An autoregressive covariance structure will be used as the primary covariance structure, given the ordered repeated measurements and the expected decrease in correlations over time. Robustness will be assessed using alternative covariance structures. The mixed-effects model uses all available observations and provides valid inference under the missing-at-random assumption. Model assumptions will be checked by residual plots and sensitivity to handling of missing data using multiple imputation. The test used is a linear contrast between the groups at post-treatment (time as categorical variable) and uses a *t*-statistic. Treatment differences will be displayed by adjusted mean differences and 95% confidence intervals. Follow-up data will be analyzed by the LMM approach taking a different contrast. The primary analysis will be performed with the ITT-population. For sensitivity additional subpopulations will be analyzed. Descriptive statistics will also be provided over time by treatment and in total. The primary parameter will also be displayed over time by a boxplot. For sensitivity also response and remission in the SOMS-7R are analyzed. Response will be operationalized as percentage improvement relative to the respective baseline score, (≥ 50% improvement within the pathological range of the SOMS-7R + 25% within the full range [93]). Remission will be coded if patients fulfill response criteria and transition from a dysfunctional to a functional score range in the SOMS-7R. As another remission criterion, we will analyze group differences in diagnostic status (SSD criteria fulfilled) at post-treatment and follow-up. Response and remission will be analyzed within a logistic regression model for each time point with the same covariates as the primary model. Descriptive statistics (absolute and relative frequencies) by time point will also be provided. Continuous secondary outcomes will be analyzed within an analysis model analogous to the primary analysis model and descriptive statistics will be given. Variables expected to have a skewed distribution like working disability days will be analyzed by Wilcoxon Rank Sum test. Categorical outcomes will be analyzed by Χ^2^-tests and will also be displayed by absolute and relative frequencies. Exploratively, health care utilization will be analyzed descriptively at the item level and compared between treatment groups. We will descriptively analyze the extent to which iSOMA is a normal part of the daily working routine of therapists’ post-treatment with the NoMAD. We will test group differences in the type and frequency of self-reported side effects in the NEQ with Χ^2^-tests and independent *t*-test for severity ratings. Potential moderators of the change processes between treatments include (a) demographics, (b) clinical characteristics (e.g., comorbidity, baseline symptom severity, traumatic experience via the CTS), as well as (c) treatment characteristics (e.g., parallel treatments, type of referral, preferences, treatment expectations via GEEE) at baseline. Mediators will be assessed at baseline, during treatment (sessions 1, 5, 10, 15), post-treatment, follow-up. We will examine the temporal, contemporaneous, and between-subject interaction of the therapists’ warmth and competence, treatment expectations, alliance, and psychotherapy outcomes with network models. To test the mechanisms of action of the blended therapy, mediating variables (self-efficacy, disability, and treatment agency) will be analyzed with structural equation modelling (SEM), assuming a lagged effect of a respective mediator on the primary outcome (dual simplex model [94]). This way, indirect effects via different pathways leading to the outcome can be examined. Model fit will be evaluated. Exploratory analyzes will examine further effect-modulating variables (e.g., treatment preferences, patient-, clinical, or treatment characteristics) as moderators (i.e., interaction effects with treatment group) or in the form of subpopulation/sensitivity analyzes (e.g., comorbidity status, treatment length, health care utilization) using the same LMMs as for the main analysis.

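### Skewed variables, and categorical outcomes other than response and remission, are tested without center or baseline; separately, SOMS-7R remission is diluted by patients who cannot meet its definition

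*Protocol article*

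**What the plan says.** Section {20a} of the protocol article (statistical methods for primary and secondary outcomes) assigns analyses by type of variable.

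- **Primary and continuous secondary outcomes:** a linear mixed model with center and baseline value among its terms.
- **Response and remission:** "Response and remission will be analyzed within a logistic regression model for each time point with the same covariates as the primary model". Those covariates include center and baseline value.
- **Skewed variables:** "Variables expected to have a skewed distribution like working disability days will be analyzed by Wilcoxon Rank Sum test".
- **Other categorical outcomes:** chi-square tests, named again for the type and frequency of side effects on the Negative Effects Questionnaire (NEQ).

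On allocation, section {16a} says: "Randomization will be stratified by study center". The outcomes section {12} has health care utilization collected at baseline, post-treatment and follow-up, and the NEQ post-treatment only.

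On SOMS-7R remission, {20a} says: "Remission will be coded if patients fulfill response criteria and transition from a dysfunctional to a functional score range in the SOMS-7R". The eligibility section {10} admits adults with SSD "who also exhibit a sufficient level of symptom severity", shown by PHQ-15 of at least 5, with disability shown by a modified PDI of at least 4. It sets no SOMS-7R threshold.

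**The concern.** There are two separate points, and they touch different outcomes.

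**Unadjusted tests.** Stratifying by center removes between-center imbalance by design, but a test that ignores center leaves the between-center variation in its error term. Where a baseline measurement exists, leaving it out also discards the variation it would explain. The same section adjusts all other efficacy outcomes for both and gives no reason for treating these differently. Precision is at stake.

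**Remission definition.** Remission requires crossing from the dysfunctional to the functional SOMS-7R range, read here as a change from baseline, as for the response criterion. Entry does not require a dysfunctional SOMS-7R score. An eligible patient may therefore start in the functional range and be a non-remitter whatever happens. At stake is how the remission rate and its difference between arms can be read. The objectives section {7} states superiority in response and remission as the third hypothesis, although {20a} introduces these analyses as a sensitivity check.

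**Working it through.** **1. The plan's own figure.** The sample size section {14} states: "we expect the difference between our blended treatment and the enhanced treatment to be *d* = 0.40 for the primary endpoint" and "with a power of 80%, and a significance level of 0.05 (two-sided), 200 patients are required, when using a t-test".

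Normal approximation: n per arm = 2(1.960 + 0.842)² / 0.40² = 98.1, so 99 per arm. The exact two-sample t-test gives 99.08, so 100 per arm and 200 in total (power 80.4%). Dropout: 200 / (1 − 0.20) = 250. The plan's numbers reproduce, and nothing below changes them.

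**2. Cost of the unadjusted rank test.** The protocol gives no baseline-outcome correlation ρ, so 0.3, 0.5 and 0.7 are assumed. As a guide, adjusting for baseline leaves a residual variance of 1 − ρ² (0.91, 0.75, 0.51). With 100 per arm and a shift of 0.4 SD, power = Φ(0.4 / √((1 − ρ²) × 2/100) − 1.96). This is 80.7% unadjusted, and 84.3%, 90.4% and 97.7% adjusted.

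The rank methods were then simulated directly: 200 evaluable patients, 8 centers of 25, a lognormal outcome, a shift of 0.4 SD on the log scale, and 2,000 runs per cell. The adjusted method was rank analysis of covariance with baseline rank and center.

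| ρ | Center SD | Wilcoxon power | Adjusted power | Gain (points) |
|---|---|---|---|---|
| 0.3 | 0 | 78.8% | 82.1% | 3.3 |
| 0.5 | 0 | 78.7% | 87.6% | 8.9 |
| 0.7 | 0 | 77.7% | 95.9% | 18.2 |
| 0.3 | 0.3 | 75.6% | 82.1% | 6.5 |
| 0.5 | 0.3 | 76.6% | 87.7% | 11.1 |
| 0.7 | 0.3 | 77.1% | 96.5% | 19.5 |

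With no treatment effect, the Wilcoxon test rejected in 3.7% to 5.3% of runs, so it is valid. The gain for center-stratified categorical tests was not simulated.

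**3. Can an eligible patient start in the functional range?** The background section {6a} describes SSD as involving one or more symptoms. Section {18a} defines the SOMS-7R index as an item mean on a 0-4 scale, with 52 items for women and 50 for men. Five symptoms at the maximum and none elsewhere give 5 × 4 / 52 = 0.38, or 5 × 4 / 50 = 0.40. Low index values are thus compatible with real illness. The functional cut-off is not in the article, so the share q who start below it is unknown.

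**4. Dilution of SOMS-7R remission.** Among all patients each arm's rate is multiplied by (1 − q), and so is the risk difference. Assumed rates among those who can remit are 20% and 35%, with 100 per arm. Power uses the usual two-proportion normal formula with pooled variance under the null.

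| q | Rates | Risk difference (points) | Odds ratio | Power, all | Power, restricted |
|---|---|---|---|---|---|
| 0 | 20 / 35% | 15.0 | 2.15 | 66.3% | 66.3% |
| 10% | 18 / 31.5% | 13.5 | 2.09 | 60.1% | 61.7% |
| 20% | 16 / 28% | 12.0 | 2.04 | 53.6% | 56.6% |
| 30% | 14 / 24.5% | 10.5 | 1.99 | 46.9% | 51.1% |

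Restriction to 100(1 − q) patients per arm recovers 1.6 to 4.2 points. With other assumed rates (20% vs 40%, 15% vs 30%) the recovery runs from 1.3 to 5.4 points. These are unadjusted comparisons; the planned model is covariate-adjusted.

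**The case against.** **On the tests.** The reach is narrow, and this stands. The named questionnaire outcomes are continuous scales and go to the adjusted mixed model. Working disability days is only an illustration and is absent from the listed secondary outcomes. Health care utilization is exploratory. The NEQ has no baseline, so only center could be used. The Wilcoxon test is valid, and the size of the gain rests on assumed correlations; an outcome with many ties at zero may gain less than the lognormal one simulated. None of this is a reason to prefer the unadjusted tests where center and a baseline are on file.

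**On remission.** The share affected may be small, since entry needs interview-confirmed SSD plus two thresholds. The odds ratio, which the planned model estimates, hardly moves. Remission by diagnostic status has no such limit. All of this stands. That baseline SOMS-7R is already a covariate helps less: one linear term on the logit scale cannot represent a remission probability of exactly zero below a cut-off.

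**Stronger readings that the documents do not support.**

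- A reader might infer that all categorical outcomes are unadjusted. Response and remission, including by diagnostic status, are modelled with center and baseline.
- A reader might infer that the logistic models use only patients observed at each visit, or are too sparse. The article does not say the first; it leaves further imputation details to the analysis plan. It gives no remission rates from which to judge the second.
- A reader might infer that the response criterion also fails for functional-range starters. That depends on how a cited source defines the pathological range, which the article does not reproduce.

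**Conclusion.** Both points hold in limited form. The rank-sum and chi-square tests, as written, ignore the randomization stratum and any available baseline. The consequence is lost efficiency, not bias or an inflated type I error. The loss for the rank test is about 3 to 20 power points, under assumed correlations of 0.3 to 0.7, a 0.4 SD shift and 200 evaluable patients. The primary endpoint, the sample size and the questionnaire outcomes are untouched.

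SOMS-7R remission, and only that endpoint, is diluted by patients who cannot meet its definition. The risk difference shrinks exactly in proportion to their share: 15 points become 13.5-12 at an assumed 10-20%, and the odds ratio moves from 2.15 to 2.09-2.04. Restricting the set regains only about 2-4 power points at 20% vs 35%, so its value lies mainly in a remission rate that can be interpreted. The true share, remission rates and correlations are not in the article.

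**What to change.** 1. **Skewed variables:** replace the plain Wilcoxon test with a center-stratified rank test (van Elteren), or with rank analysis of covariance including center where a baseline value was collected.
2. **Categorical outcomes other than response and remission:** replace plain chi-square tests with center-stratified Cochran-Mantel-Haenszel tests. For the NEQ, stratify by center only.
3. **SOMS-7R remission:** name the functional cut-off and report remission in patients who are in the dysfunctional range at baseline, beside the all-randomized result. The set is defined before randomization, so the comparison between arms stays randomized. Report how many patients in each arm start in the functional range.

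The response definition and the covariates of the logistic models need no change on this account.

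The cost is wording, fixed before the database is locked and the analysts are unblinded. It needs no new data and uses standard procedures. The downside is a slightly smaller denominator for the restricted remission analysis.

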
### Interim analyzes {21b}

Not applicable since there will be no interim analysis regarding the main objective of the trial.

### Methods for additional analyses (e.g., subgroup analyses) {20b}

Subpopulation analyses will be performed by LMMs similar to the primary analysis model with additional covariates. Subpopulations will be investigated by analyzing the interaction term of the subpopulation and treatment group to optimize treatment selection for individual patients. The determination of the Minimal Clinically Important Difference for the SOMS-7R will be done precision based (using the Standard Error of Measurement), distribution based (0.5 Standard Deviation), and anchor based [95, 96]. To test robustness of effects, we will examine LMMs for the following sample: patient per protocol: regularly completed therapy and primary outcome completed at baseline, end of therapy, and 6-month follow-up.

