### Strategies to improve adherence to interventions {11c}

Both interventions are manualized, and therapists will be trained in both treatment forms. All treatments are video- (or audio-)taped and - in case of trainee therapists - continuously supervised (approximately every fourth session) by licensed supervisors experienced in the CBT rationale [51]. Licenced psychotherapists will schedule regular intervision groups. Adherence and engagement with the online modules will be automatically assessed within the platform. Therapists can monitor their patients’ platform usage (e.g., lecture/diary completion) and address potential issues in personal sessions. In the control group, patients will report their use of the self-help booklet regularly during the treatment process. Treatment integrity will be video- (or audio-)registered and rated after completion of the treatments using the method of assessing treatment delivery (MATD) in clinical trials [60]. Although therapists deliver both treatment forms, treatment contamination can practically be ruled out since therapists cannot alter the add-on (iSOMA vs. self-help booklet). Patients in the intervention group receive automatic e-mail notifications if a new module has been assigned to them or if they have not completed a module within ten days.

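### The per-protocol set requires the 6-month score even for the post-treatment contrast and has no criterion for add-on use; treatment length, a post-randomisation variable, is listed as a subpopulation

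*Protocol article*

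**What the plan says.** Section {20b} of the protocol article introduces one sample for the robustness check, "To test robustness of effects, we will examine LMMs for the following sample", and defines it as "patient per protocol: regularly completed therapy and primary outcome completed at baseline, end of therapy, and 6-month follow-up". The rule names no iSOMA module or booklet chapter. Add-on use is nevertheless recorded in both arms under {11c}: "Adherence and engagement with the online modules will be automatically assessed within the platform" for iSOMA, and regular patient self-report for the booklet.

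Section {20a} places the primary test at post-treatment, in all randomised patients, with a mixed model that uses every available observation under missing at random. Multiple imputation is the missing-data sensitivity analysis ({20c}).

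On subpopulations, the sentence in {20a} that begins "Exploratory analyzes will examine further effect-modulating variables" includes work "in the form of subpopulation/sensitivity analyzes (e.g., comorbidity status, treatment length, health care utilization) using the same LMMs as for the main analysis". Section {20b} gives the method and aim: "Subpopulations will be investigated by analyzing the interaction term of the subpopulation and treatment group to optimize treatment selection for individual patients". The moderators named in {12} and {20a} are taken at baseline.

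**The concern.** Three separate things look wrong.

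- **Selection on a later outcome.** Whether a patient returns a questionnaire six months after treatment says nothing about whether treatment followed the protocol. Making it a condition of the set removes valid post-treatment data, and if return depends on how the patient fared, and does so differently by arm, it distorts the contrast that the set is meant to check. A gap between this analysis and the intention-to-treat result could then come from the check itself.
- **No criterion for the randomised component.** Both arms receive the same 20 CBT sessions; only iSOMA versus booklet differs. A set defined by completed therapy describes adherence to the part that the arms share.
- **A subgroup variable formed after randomisation.** Treatment length depends on extra sessions (up to four), continuation ({6b}) and discontinuation ({11b}). All occur after allocation and may respond to the arm or to the outcome. Length is also unknown when a treatment is chosen, so it cannot serve the stated purpose of "analyzing the interaction term of the subpopulation and treatment group to optimize treatment selection for individual patients".

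At stake is how far the robustness and subgroup results can be trusted, not the confirmatory test.

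**Working it through.** **The plan's own figure.** From {14}: d = 0.40, two-sided 5%, 80% power, t-test. The noncentral t gives 99.08 per arm, rounded up to 100, total 200. Then 200 / (1 − 0.20) = 250. Both stated numbers reproduce; power at 100 per arm is 0.804.

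**Precision lost through the 6-month condition.** Start from the 100 per arm with a post-treatment score that the plan expects. The document gives no rate of loss between post-treatment and follow-up; assume 12%. Then 88 per arm remain. The standard error rises by √(200/176) = 1.066, about 7%, and t-test power at d = 0.40 falls from 0.80 to 0.75.

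**Bias at post-treatment.** Simulation with no true effect, 100 per arm with a post-treatment score, and 12% follow-up loss in each arm. Loss is logistic in the post-treatment score (slope per SD; 0.7 and 1.0 are odds ratios of 2.0 and 2.7). Baseline adjustment assumes a correlation of 0.6 between baseline and post-treatment. All these inputs are assumptions; 20,000 runs per row.

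| Slope iSOMA+ / CBT+ | Bias, unadjusted (SD) | Rejection | Bias, baseline-adjusted (SD) | Rejection |
|---|---|---|---|---|
| 0 / 0 | 0.00 | 5% | 0.00 | 5% |
| 0.7 / 0 | −0.08 | 8% | −0.05 | 7% |
| 1.0 / 0 | −0.11 | 11% | −0.07 | 9% |
| 1.0 / 0.7 | −0.03 | 5% | −0.02 | 5% |
| 0.7 / 0.7 or 1.0 / 1.0 | 0.00 | 5% | 0.00 | 5% |
| 0 / 1.0 | +0.11 | 11% | +0.07 | 9% |

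Higher scores are worse, so a negative sign favours iSOMA+. The bias can run either way and vanishes when the dependence is the same in both arms. In every row the post-treatment score is observed for all 200 patients, so a model that keeps them all has no such bias.

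**Dilution from non-use.** If a share u of iSOMA+ patients in the set use the modules and non-users gain nothing from them (assumed), the contrast is 0.40 × u: 0.36, 0.28 and 0.20 at u = 0.9, 0.7 and 0.5. This is a different quantity being estimated, not selection bias.

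**Treatment length.** With normal variables and a median split, the long-minus-short difference in outcome within an arm is 2ρ√(2/π), where ρ is the correlation of length with outcome. The apparent interaction is 2(ρ₁ − ρ₂)√(2/π). For ρ₁ = +0.2 and ρ₂ = −0.2 it is 2 × 0.4 × 0.798 = 0.64 SD; for ±0.1 it is 0.32 SD; for equal correlations it is zero. The formula shows that an interaction can appear without true effect modification. It does not show that one will.

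**The case against.** The strongest defence is about scope. The primary analysis is intention-to-treat with all available data, backed by 100 imputed datasets. The per-protocol analysis is one robustness check, and treatment length is an example in a sentence marked exploratory. No confirmatory conclusion rests on either. This stands and limits the weight of the point.

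A reader might infer that these analyses do give biased answers. The documents do not support that: they give no figure for follow-up loss or for its relation to outcome by arm, and equal dependence produces no bias. Likewise 0.64 SD should not be read as an expected spurious interaction, because it restates the opposite-sign correlations put into it, and nothing in the protocol suggests opposite signs.

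A reader might also infer that patients who open no module will be counted as per protocol. The rule as written does not exclude them. However, therapists activate the modules and can follow their use, and persistent non-compliance can end the allocated intervention ({11b}). Exact thresholds are properly left to the SAP.

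A set based on add-on use would itself be selected after randomisation, and measured by platform log in one arm and self-report in the other. So it is not a clean replacement.

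Finally, health care utilization is not shown to be a post-randomisation subgroup variable: it is also measured at baseline, and {20a} gives no time point for this use.

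What remains is the stated 6-month condition, the missing link to the randomised component, and treatment length as an interaction subgroup. None of these is a detail left open for the SAP: the first two lie in a definition the article states, and the third is a variable it names.

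**Conclusion.** The point holds in limited form. The 6-month condition excludes usable post-treatment data and makes the mixed model in effect a complete-case analysis at the three main assessments. The loss of precision is certain if any therapy completer with a post-treatment score lacks the follow-up score. Bias is possible, in either direction: up to about 0.1 SD with 12% loss that depends on outcome in one arm only, 0.05 to 0.07 SD after baseline adjustment, and about nil with equal dependence. Against a planned effect of 0.40 SD this is enough to blur a robustness check.

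The absence of an add-on criterion means that the set does not measure adherence to the randomised contrast. Treatment length cannot support treatment selection, whatever its estimated interaction. All sizes rest on the stated assumptions. This is a correction that should be made, but it does not threaten the primary result.

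**What to change.** 1. Define the per-protocol set by treatment received. Remove the 6-month condition and any other post-baseline outcome-completeness condition, and keep every member in the mixed model with whatever data are available.
2. Restrict treatment-by-subgroup interactions to variables measured before randomisation, and state that health care utilization enters at its baseline value.
3. Report results by treatment length descriptively only, outside the treatment-selection aim.
4. Optionally, add a supportive analysis by recorded module or chapter use, labelled as non-randomised and measured differently by arm.

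The cost is wording in the protocol and SAP. No new data are needed. Recruitment is planned until August 2027 and analysts stay blinded until database lock, so the change can still be prespecified credibly. The drawback is that booklet use is self-reported, so the optional analysis in item 4 is weaker in the control arm.
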